#### Body feelings questionnaire

Per participant, a total of six questionnaires will be filled [(Experiment 1 + Experiment 2) × (3 feedback conditions: ‘ascendent’, ‘constant’, ‘descendent’)]. We will use Google form for data collections and, to ensure the confidentiality and security of participant information, data will be moved to a secure server linked to the university, with encryption and other security measures in place. All participant-related data will be stored by using research identification numbers/codes that uniquely identify each user and will furthermore be password-protected to ensure the privacy of the participants. The sheets will be organized and imported into Microsoft Excel 2021 and subsequently into the statistical software IBM SPSS Statistics version 28.0. By default, we don’t expect missing values.

#### Body visualizer task

The degree of body size discrepancy will be hand-coded by the experimenter into a data sheet. Per participant, a total of four summary estimations will be calculated [(baseline body size discrepancy) + (post-experiment body size discrepancy × 3 feedback conditions: ‘ascendent’, ‘constant’, ‘descendent’)] according to the BPI index (see Table 1 for more details).

### Descriptive statistics

For the final sample, data will be expressed and pulled as means and standard deviations for parametric data whereas median and interquartile range will be used for non-parametric data. Additionally, skewness, and kurtosis for the continuous variables and frequency counts and percentages for the categorical variables will be reported. Cronbach’s α for each questionnaire will be reported for each questionnaire.

### Sample size considerations

As these analyses are intended to generate future confirmatory hypotheses, no sample size calculation was conducted. As Jones et al. [53] noted, sample size calculation may be of little value in early exploratory studies where there is a lack of previous research. In an exploratory study, the primary focus is on generating new research questions, identifying patterns and trends, and identifying potential areas for further research, rather than on testing a specific confirmatory hypothesis. As such, the sample size in an exploratory study may not be determined based on statistical power or precision and could be relatively small. Instead, the sample size may be based on the need to obtain a sufficient amount of data to allow for the exploration and identification of meaningful patterns and trends.

In this regard, a total of 100 participants (50 participants in each group) will allow us to gain an exploratory understanding between body perception and non-naturalistic auditory information in participants with subthreshold ED symptomatology. This sample size is the minimum recommended by Brysbaert [54] to seek differences between groups and is also between 30 and 150 participants, that is the sample size usually recommended in exploratory study designs with non-probability sampling [55]. To this end, and based on norms for the Spanish version of the Eating Disorders Examination Questionnaire (S-EDE-Q), we will screen approximately at least 450 young adult females [39].

Due to the limited sample size, we acknowledge that the statistical power for each of the hypotheses proposed in this study to detect differences between groups might not be sufficient according to the traditional standards in experimental psychology (effect size = 0.4, power = 0.80 and alpha value = 0.05) [54]. Therefore, the results should be taken with caution and should be contextualized within an exploratory framework. In case of meaningful results, the present exploratory study will provide the necessary foundation for a formal sample size calculation for a future confirmatory larger-scale study.

### Statistical analyses

#### Primary aim: auditory-driven changes in body perception Baseline measures

To determine differences between the groups, analyses will be performed with a Student's t-test paired comparison (for normal distribution) or Wilcoxon tests (for non-normal distribution) for ED symptomatology (EDE-Q), interoceptive body awareness (MAIA), sensory-processing sensitivity (HSPS) and body size discrepancy (Body visualizer tool).

#### Experiment 1 and Experiment 2

For the estimations of body part position/size, confidence task and items from the body feelings questionnaires we will follow a 2 × 3 ANOVA within-between interaction repeated-measures design (see Table 2). Specifically, we will use non-parametric ANOVAs on aligned rank (ART) data, suitable for ordinal data, using the R package ARTool [56]. The ANOVAs will involve a group factor with 2 levels (subthreshold EDs and controls) and a feedback condition factor with 3 levels (‘ascendent’, ‘constant’, ‘descendent’). Prior the analysis, assumptions of independence, normality and sphericity will be checked. As in [24], we will include the degree of body size discrepancy as covariate in case of significant baseline differences. Appropriate post-hoc tests will be conducted in case of significant differences.

**Table 2 Tab2:** ANOVA 2 × 3 design

Group	Feedback condition		
	Ascendent	Constant	Descendent
Subthreshold EDs	Subthreshold EDs–Ascendent	Subthreshold EDs–Constant	Subthreshold EDs–Descendent
Controls	Controls–Ascendent	Controls–Constant	Controls–Descendent

For body size discrepancy, we will follow a 2 × 3 ANOVA within-between interaction repeated-measures design (see Table 3). The ANOVAs will involve a group factor with 2 levels (subthreshold EDs and controls), a time factor with two levels (baseline and post-experiment) and a feedback condition factor with 3 levels (‘ascendent’, ‘constant’, ‘descendent’).

**Table 3 Tab3:** ANOVA 2 × 2 × 3 design

Group	Baseline	Experiment		
		Feedback condition		
		Ascendent	Constant	Descendent
Subthreshold EDs	Subthreshold EDs Baseline	Subthreshold EDs Post-experiment Ascendent	Subthreshold EDs Post-experiment Constant	Subthreshold EDs Post-experiment Descendent
Controls	Controls Baseline	Controls Post-experiment Ascendent	Controls Post-experiment Constant	Controls Post-experiment Descendent

The degree of body size discrepancy as covariate will be included in case of significant baseline differences. Similarly, assumptions of independence, normality and sphericity will be checked and post-hoc tests will be conducted if appropriate.

Following a similar approach as in [24], the proposed analysis will be based on the division of the controls vs. sub threshold group based on scores falling above or below the cut off of 2.8 on the EDE-Q. A complementary, secondary correlational analysis will be performed between estimation of body position/size measures and EDE-Q scores considering the entire sample.

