## Participants

The experiment will be conducted individually in a quiet laboratory room [see Additional file 1, section A]. In keeping with previous literature and to facilitate the comparison and interpretation of the results because of the variability shown in related measures, the sample will comprise young adult females (sex assigned at birth) in the 18–24 age range, where the prevalence of EDs in this population is the highest [34]. However, it should be pointed out that previous evidence has reported high prevalence of EDs not only in female samples but also in other populations such as in men or gender diverse individuals [35–37]. Additionally, we decided to focus on the waist because this body part has been shown to be particularly emotionally salient for females and a reliable indicator of body mass index (BMI) [4, 38]. Participants will be recruited through public advertisements and social media posts (convenience sampling) and they will be paid or compensated with grade points for their time. To split the sample into participants with and without ED symptomatology, the Spanish Eating Disorder Examination Questionnaire (S-EDE-Q) [39]) will be administered (see Table 1 for more details). The pre-screening will allow to form two groups of similar size: once the desired participant sample size has been reached for one of the groups, only participants falling into the other group defined for the study will be invited to take part. The S-EDE-Q have demonstrated good psychometric properties in young female adults in Spain [39]. A global EDE-Q score ≥ 2.8 has been shown to provide an optimal trade-off between sensitivity and specificity when it is used for screening in primary care [40]. Available resources for participants will include psychoeducation and support for body image and eating-related concerns, provided by a team member. The availability of these resources will be specified in the informed consent. Moreover, to not assume that all individuals are cis-gender, gender identity will be assessed through an additional question.

**Table 1 Tab1:** Overview of study measures and data collection timepoints

Measure	Description	Baseline	Experiment	
			1	2
Demographic data	Participants’ age. In addition, BMI will be calculated with the following formula: BMI = weight (kg)/(height (m)^2^) following the World Health Organization’s criterion [45]	X		
Information consent	Written informed consent	X		

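### A paired t-test, or an unspecified Wilcoxon test, is named for comparing two independent, unmatched groups at baseline

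*Protocol article*

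**What the plan says.** In the protocol article, Statistical analyses, under the baseline measures of the primary aim, the stated purpose is to find differences between the groups. The method given is a Student's "t-test paired comparison (for normal distribution) or Wilcoxon tests (for non-normal distribution) for ED symptomatology (EDE-Q"). The other variables are "interoceptive body awareness (MAIA), sensory-processing sensitivity (HSPS) and body size discrepancy (Body visualizer tool").

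The groups are defined in three places:
- Participants: "The pre-screening will allow to form two groups of similar size". Once one group is full, only women who fall into the other are invited.
- Sample size considerations: "a total of 100 participants (50 participants in each group").
- Statistical analyses: "the division of the controls vs. sub threshold group based on scores falling above or below the cut off of 2.8 on the EDE-Q".

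For the experimental outcomes the same section uses a "2 × 3 ANOVA within-between interaction repeated-measures design", with group and feedback condition as its two factors. The baseline result is then used again: "The degree of body size discrepancy as covariate will be included in case of significant baseline differences".

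**The concern.** A paired test needs a link between each value in one group and one value in the other. Here the two groups are different people, balanced in number only. Software told to run a paired test would link participants by their position in the data file. The p-value would then reflect an arbitrary ordering as well as the data.

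Two things hang on it. Baseline body size discrepancy is a natural measure for H1, which asks whether the groups differ in body image distortion. And the significance of that same comparison decides whether body size discrepancy enters the ANOVAs as a covariate, so an order-dependent p-value could select the model used for the primary aim.

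**Working it through.** **1. Is there any pairing the text could mean?**
- Matched pairs of women: none described. Recruitment fills each group to a number.
- Repeated measures within a woman: Table 1 places EDE-Q, MAIA and HSPS at baseline only. Baseline body size discrepancy is one value per woman, the average of two avatar adjustments. There is no second value to pair for this comparison.
- The ANOVA design in the same section treats group as between-subject.

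The word *paired* therefore contradicts the plan's own design.

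**2. No figure to reproduce.** The article states that no sample size calculation was done. The numbers below are illustrative. They use 50 per group, two-sided alpha 0.05 (the article gives alpha 0.05 but not sidedness), and the effect size of 0.4 that the article cites as a conventional standard.

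**3. Why row order changes p.** With n per group, equal SDs and an observed standardised difference d:
- independent test: t = d√(n/2), on 2n − 2 = 98 df
- paired test: t = d√(n/2) / √(1 − r), on n − 1 = 49 df

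Here r is the correlation produced by whichever rows happen to sit side by side. Over random orderings r has mean 0 and SD 1/√(n − 1) = 1/√49 = 0.143.

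With d = 0.4 and n = 50, the independent t = 0.4 × √25 = 2.00, so p = 0.048 in any row order. For the paired test:
- r = 0: t = 2.00, p = 0.051
- r = +0.28: t = 2.00/√0.72 = 2.36, p = 0.022
- r = −0.28: t = 2.00/√1.28 = 1.77, p = 0.083

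Simulation on one data set of this kind (10,000 row orders) agrees. The paired p ran from 0.005 to 0.116, its central 95% was 0.022 to 0.083, and 47% of orders gave p < 0.05. The signed-rank p (3,000 orders) ran from 0.002 to 0.194, with 55% below 0.05. The rank-sum p was 0.024 in any order.

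**4. How this depends on the correct p.** The paired test is significant when r > 1 − (t/2.0096)², where t is the independent statistic and 2.0096 is the 5% critical value on 49 df. Dividing by 0.143 and using the normal curve gives the expected share; simulation used 20 data sets with 1,000 pairings each.

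| Correct p | t (98 df) | r must exceed | Expected share of orders with p < 0.05 | Simulated |
|---|---|---|---|---|
| 0.001 | 3.393 | −1.85 | 100% | 100% |
| 0.01 | 2.627 | −0.71 | 100% | 100% |
| 0.05 | 1.985 | 0.025 | 43% | 43% |
| 0.10 | 1.661 | 0.317 | 1.3% | 1.2% |
| 0.20 | 1.290 | 0.588 | <0.01% | 0% |
| 0.50 | 0.677 | 0.887 | <0.01% | 0% |

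The 47% in step 3 belongs to a correct p of 0.048 and the 43% to exactly 0.05. The effect is concentrated near the threshold.

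**5. Long-run properties (simulated).**
- Random pairing: type I error 0.050 for both tests; power at d = 0.4 is 0.50 paired against 0.51 independent.
- Both groups' rows sorted on a variable correlated 0.3, 0.5 or 0.7 with the outcome: paired type I error 0.057, 0.087 and 0.155.

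**6. Unequal groups.** A paired test uses at most min(n₁, n₂) rows from each group. The Data management section removes from all analyses any participant with more than one excluded trial per condition. That may leave unequal groups; the article gives no expected rate.

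**The case against.** The strongest reply is that this is a drafting slip with small consequences. The sentence itself speaks of differences between groups, the ANOVAs handle group correctly, and every hypothesis is declared exploratory. Much of this stands, and it limits what may be inferred.

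- A reader might infer that the test has no valid meaning. That goes too far: the mean difference is the same, and random pairing preserves the type I error with almost no loss of power. Inflation needs sorted rows, and the article describes no such sorting.
- A reader might take 43% to 47% as the general chance of a false or flipped result. It holds only where the correct p is about 0.05. EDE-Q defines the groups, so its comparison is not in doubt.
- A reader might call this the test of H1. The plan does not say so, and the ANOVA laid out in Table 3, with group as a factor, also bears on H1.
- Wilcoxon could mean rank-sum, which would be right. Beside *paired* it reads as signed-rank, so the text is ambiguous rather than plainly wrong on that half.
- The exclusion rule may, not must, make the groups unequal.

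None of this repairs the t-test wording. Nothing elsewhere in the article corrects it, and an analyst who followed it would run the wrong procedure.

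**Conclusion.** The point holds in limited form. The named t-test does not fit two independent, unmatched groups, and the Wilcoxon type needs stating. The practical damage is a p-value that depends on file order, with three consequences: an unstable decision when the correct p is close to 0.05, inflated error if both groups are sorted on something related to the outcome, and lost participants if group sizes end up unequal. It matters beyond a descriptive baseline table because the body size discrepancy comparison bears on H1 and controls the covariate rule. The sizes given assume 50 per group, equal SDs, approximately normal data and two-sided alpha 0.05. The exploratory framing lowers the stakes but does not make a paired test suitable, so it should be corrected before analysis.

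**What to change.** Replace the baseline test wording with: *independent-samples t-test (for example Welch), or Mann-Whitney U / Wilcoxon rank-sum test where distributions are clearly non-normal*. Apply it to all four baseline variables, including the body size discrepancy comparison that feeds the covariate rule. Reporting the mean difference with a 95% confidence interval would be useful but is not needed to cure the defect. The cost is one sentence of plan text, with no change to recruitment, sample size or data collection.

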MAIA§	To measure interoceptive body awareness. Self-administered questionnaire composed of 32 items using 6-point Likert scales ranging from 0 (never) to 5 points (always). Eight subscales are measured, including: (1) noticing (3 items); (2) not-distracting (2 items); (3) not-worrying (2 items); (4) attention regulation (7 items); (5) emotional awareness (5 items); (6) self-regulation (4 items); (7) body listening (3 items) (8) trusting (3 items). It generates a total direct score that ranges from 0 to 160 points. Higher scores indicate higher interoceptive awareness. A total global score will be obtained by averaging the six subscales. The MAIA have shown adequate internal consistency (Cronbach’s alpha 0.64 to 0.83 for all subscales)	X		
Auditory trials	Presented in four conditions: an anchor task (20 trials); a practice task (3 trials); an experimental block (30 trials) and a questionnaire block (3 trials)		X	X
Estimation of body position (finger/waist)	To assess estimation of location or position of fingertip/knuckle (allowing to calculate the estimated finger length can be calculated) and waist width after each auditory experimental trial		X	
Confidence task	It has been found that the reliability of perception might be linked to subjective rather than objective accuracy [41]. For example, previous studies using body illusions report that confidence was not accompanied by increases in objective accuracy (i.e., [42, 43]). Therefore, to assess the reliability of their estimations, after each auditory experimental trial, the feeling of confidence with the estimation of body part position will be explicitly assessed by asking the participants: “From one to seven, how confident are you of your estimation?” (7-point Likert scale)		X	X
Body feelings questionnaire (finger/waist) [25]	To assess subjective feelings about their finger/waist after the trials (susceptibility to the illusion). Participants will respond to a questionnaire containing 7-point Likert-type response items ranging from 1 (strongly disagree) to 7 (strongly agree) (Finger: 14 items; Waist: 13 items). In addition, a range of figures representing finger/waist will be presented. Each figure shows a whole hand/trunk selectively shrunk or elongated. Participants will be asked to choose one of the figures to describe the subjective feeling of the size of their finger/waist when listening to the sound. [see Additional file 2 and 3 for more details]		X	X

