The experimenter will use the measurements on the back of the ruler to record the fingertip and knuckle positions, rounding to the nearest 0.5 cm. After each trial, the clips are relocated. After completing the practice task, the experimental block will begin. Participants will repeat the task for thirty trials. Each experimental tone will be presented ten times. The order of trials will be randomized across participants. Participants will be given the opportunity to rest after each 10 trials.

After the experimental block, participants will be asked to repeat the task for three more trials (one for each sound condition, their order randomized across participants), in order to collect self-report measures (questionnaire block). After each trial, participants will complete a questionnaire that assesses their subjective experience during the task [see Additional file 2].

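### Aligned-rank ANOVA is fixed for the 27 single 7-point questionnaire items as suited to ordinal data, but its group and group-by-tone tests can over-reject when answers concentrate in one category

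*Protocol article*

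**What the plan says.** The section on Experiment 1 and Experiment 2 under Statistical analyses names the outcomes: "For the estimations of body part position/size, confidence task and items from the body feelings questionnaires we will follow a 2 × 3 ANOVA". It then fixes the method: "we will use non-parametric ANOVAs on aligned rank (ART) data, suitable for ordinal data, using the R package ARTool". The design crosses "a group factor with 2 levels (subthreshold EDs and controls") with "a feedback condition factor with 3 levels".

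Table 1 gives the body feelings questionnaire as 7-point agreement items ("Finger: 14 items; Waist: 13 items"), so 14 + 13 = 27. The procedure for Experiment 1 collects these answers in "three more trials (one for each sound condition, their order randomized across participants"), and Experiment 2 does the same. Each participant therefore gives one answer per item and tone. The position, size and confidence data differ: Data management averages them over ten repetitions per tone.

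The article gives no expected distribution of the answers, no check on how concentrated they are, and no alternative analysis for these items. The method and its justification are both stated in the text, so this is not a detail left to an unseen analysis plan.

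**The concern.** The aligned rank transform (ART) removes the estimated cell means, adds back the one effect under test, and ranks the result. On a coarse scale, people who gave the same answer in different group-by-tone cells then no longer have the same value. Chance differences in cell means, however small, put all those who answered 1 in one cell above or below all those who answered 1 in another. The F test on the ranks partly reads this block order as an effect.

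The abstract makes the questionnaires the explicit measure of illusion strength. H2 to H4 are claims about group or group-by-tone differences, and those are the two tests that can be inflated. H3 looks for unusual patterns in the subthreshold group, so a spurious interaction could pass as support for it. The sample size section says that meaningful results will be the foundation for a later confirmatory study.

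**Working it through.** **Plan's own figure.** The article states no type I error for ART, so there is nothing to reproduce.

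**Inputs from the article.** 2 groups of 50, 3 tones, one 7-point answer per person, item and tone; hence 2 × 50 × 3 = 300 answers per item. The sample size section mentions an alpha of 0.05 only as a traditional standard; it is used here as the nominal level.

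**Assumptions, not in the article.** The answer distribution, and a within-person correlation from 0 to 0.8. Answers were made by cutting a correlated latent normal variable into seven categories.

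**What alignment does.** With cell mean c(ij), group mean g(i), tone mean t(j) and grand mean m, the value ranked is:

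- group test: Y − c(ij) + [g(i) − m]
- group-by-tone test: Y − c(ij) + [c(ij) − g(i) − t(j) + m] = Y − g(i) − t(j) + m

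In both, every answer in a cell is shifted by the same cell-specific amount. If p(k) is the share of answers in category k, a tiny difference in shift between two cells of 50 with the same distribution separates their mean ranks by 50 × Σp(k)²:

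- uniform answers: 50 × 7 × (1/7)² = 7.1 ranks
- 50% at 1 (0.50, 0.20, 0.12, 0.08, 0.05, 0.03, 0.02): 50 × 0.3146 = 15.7 ranks
- 70% at 1 (0.70, 0.12, 0.07, 0.05, 0.03, 0.02, 0.01): 50 × 0.5132 = 25.7 ranks

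So concentration in one category drives the problem, not ties as such. A uniform item also has about 300/7 ≈ 43 tied answers per category.

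**Simulation.** Aligned values were mid-ranked and put through a split-plot ANOVA, reading only the aligned effect: group F on 1 and 98 df, interaction F on 2 and 196 df. The steps were coded directly; the ARTool package itself was not run. There were 4,000 to 10,000 replicates per scenario, so the Monte Carlo standard error near 5% is about 0.2 to 0.35 points.

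Rejection rates of true nulls, no effect of any kind, correlation 0.3 and 0.6:

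| Answers | ART group | ART group-by-tone |
|---|---|---|
| Uniform | 5.4–5.8% | 5.3–5.4% |
| Bell, 32% in the modal category | 6.5–7.3% | 5.7–6.6% |
| Skewed, 35% at 1 | 6.8–7.6% | 6.4–6.7% |
| 40% in one category | 7.6–8.6% | 6.5–7.5% |
| 50% | 9.7–11.4% | 8.1–9.8% |
| 60% | 13.0–16.4% | 10.2–12.2% |
| 70% | 20.9–24.8% | 15.1–17.7% |
| 80% | 32.1–37.1% | 23.6–25.2% |

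Over the whole correlation range 0 to 0.8, spread-out answers (uniform, bell, skewed, U-shaped) gave 5.0–9.0% for group and 5.3–7.7% for the interaction. At zero correlation the group test was worse for floor items: 15.4% with 50% at 1 and 29.0% with 70%.

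Same tone effect in both groups (latent shifts +0.5, 0, −0.5), so that group and interaction are still null. Shares are before the shift:

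| Answers | ART group | ART group-by-tone |
|---|---|---|
| Uniform | 5.7–6.3% | 5.4–6.0% |
| Bell | 5.8–6.4% | 5.5–7.1% |
| Skewed, 35% at 1 | 7.8–10.0% | 9.5–11.9% |
| 50% at 1 | 11.4–13.4% | 14.3–17.2% |
| 70% at 1 | 23.2–27.2% | 24.8–29.8% |

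With shared tone effects of 0.5 to 0.8 latent SD and 50% at 1, the rates were 12–14% (group) and 16–18% (interaction).

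**Comparators.**

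- An ordinary mixed ANOVA on the raw 1–7 scores rejected 4.2–6.1% in every complete-null scenario. With the shared tone effect it rejected 4.3–5.9% for group and interaction. The excess therefore comes from aligning and ranking, not from the discrete scale.
- The ART tone main effect stayed at 4.7–9.3% under the complete null.
- ART on continuous data gave 4.8–5.0%, and on ten-trial means of estimates rounded to 0.5 cm 4.4–5.2%.
- The ten-trial averages of the confidence ratings were not simulated.

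**The case against.** The strongest objection is that the deciding input is missing. The item wording is in additional files that are not shown, and no answer distribution is given. Whether any item has half its answers in one category, and how many do, is unknown. With well-spread answers and no effect the inflation is small. This stands: it limits what can be said about size, though not about the mechanism.

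A reader might infer that the method doubles the false-positive rate for all 27 items, or that any ties invalidate it. The documents do not support either. Under a complete null, doubling needs about half of the answers in one category for the group test and about 60% for the interaction. Less suffices for the interaction when a tone effect is present: about 10 to 12% at a 35% modal share.

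The second objection is the exploratory framing. All hypotheses are declared descriptive-exploratory, the sample size section asks for caution, and the position and size estimates give an unaffected second measure of the illusion. This lowers the priority. It does not remove the point, because the caution in that section concerns low power, not false positives. The shared-tone-effect scenario is also a realistic one, since the Background expects the illusion to occur for both finger and waist.

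**Conclusion.** The concern holds in conditional form and should be fixed; the exploratory purpose keeps it from being critical. ART is not safe as a blanket choice for single 7-point items, and the unqualified statement that it suits ordinal data is too broad. With 50 per group, the group and group-by-tone tests run at about 5 to 9% for spread-out answers with no effect. With half the answers at 1 they run at about 8 to 12% with no effect and about 12 to 18% with a shared tone effect. With 70% at 1 they run at about 15 to 30%.

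The floor-item figures rest on assumed distributions, a within-person correlation of about 0.3 to 0.6, and a direct coding of the ART steps. A reader should not extend the point to the tone main effect, which is little affected under a complete null, or to the averaged centimetre estimates, which are not affected.

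**What to change.** Remove the statement that the method suits ordinal data. For the 27 single items, replace ART with one of two analyses, named in advance:

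- a cumulative-link (ordinal) mixed model with group, tone and group-by-tone over all three tones and a participant effect. Its error rate was not simulated here; or
- an ordinary mixed ANOVA on the 1–7 scores, which held its level in the simulations above.

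Do not reduce each item to one ascending-versus-others contrast compared by a Mann-Whitney test. H3 allows effects outside the ascending tone, and such a contrast cannot see them. When the groups were made to differ only between the constant and descending tones, that test rejected 5.4% (uniform item, ±0.3 latent SD) and 4.9% (50% at 1, ±0.4). The ordinary ANOVA rejected 69.6% and 81.1%.

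The change is a sentence or two in the analysis plan and needs no new data. R is already in use for ARTool. The cost is slightly more analysis work and possible convergence problems for very sparse items, so the plan should say what happens if the ordinal model does not converge.
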